## Abstract

**Background:**

Monochorionic twin pregnancies are at increased risk of complications due to sharing a single placenta and potentially developing unbalanced vascular anastomoses. Complications include twin-twin transfusion syndrome (TTTS) which affects 10–15% monochorionic twins, and if untreated has a 70–90% perinatal loss rate. We are currently unable to predict which twins will develop complications or to what severity. We have previously shown differences in angiogenic and placental growth factors in maternal blood in pregnancies complicated by TTTS compared to twin pregnancies not complicated by TTTS but matched for gestation. There is also evidence to suggest that abnormal ultrasound measurements recorded in the first trimester (nuchal translucency and crown-rump length) may be associated with severe TTTS later in pregnancy, however the detection rate is only reported as 52%. We hypothesize that if these changes precede the development of the clinical syndrome, this may increase the sensitivity and specificity of detecting adverse pregnancy outcomes.

**Methods:**

This cohort study has retrospective and prospective elements. In the retrospective cohort we will measure factors (decided based on preliminary work and a systematic review and meta-analysis) in stored maternal blood samples taken in the first-trimester, extract first-trimester ultrasound measurements and match these to pregnancy outcome. The prospective cohort will be divided into a “screening” cohort and “complicated” cohort. The screening cohort will undergo serial maternal blood sampling at 12, 16 and 20 weeks; we will extract ultrasound measurements and match to pregnancy outcome. The complicated cohort will comprise of women referred to the Fetal Medicine Centre with complications of monochorionicity. If the decision is taken to undergo fetoscopic laser ablation we will take maternal blood samples and amniotic fluid samples pre- and post-laser treatment. The same factors will be measured in the prospective cohort as informed by the retrospective study.

**Discussion:**

This study aims to increase knowledge surrounding the pathology of complications in monochorionic twins, to aid future diagnosis and management.

**Trial registration:**

ISRCTN 13114861 (retrospectively registered)

## Background

All twin pregnancies have increased risk over singletons, with monochorionic (MC) twins demonstrating the highest risk. Thirty per cent of twins are MC, but they experience 75% of all twin complications, the pathologies of which are closely linked to the fact that they share a single placenta and thus can develop unbalanced vascular anastomoses [1]. Complications that are specific to monochorionicity include twin-twin transfusion syndrome (TTTS), selective intrauterine growth restriction (sIUGR) and twin anaemia polycythaemia sequence (TAPS) [2]. TTTS complicates 10–15% of MC twins and usually occurs between 15 and 26 weeks. At present, the prognosis is dependent upon early treatment and method of treatment: if untreated it is associated with a perinatal loss rate of 70–90%. A staging system, the Quintero system, exists but correlates poorly with outcome [3]. Even with apparently ‘successful’ antenatal treatment (with fetoscopic laser ablation (FLA)), TTTS is still associated with 10% neurological morbidity. We are currently unable to accurately predict which twins will develop complications or how severe they will be. There is some evidence that first trimester ultrasound screening of MC twin pregnancies between 11 and 13^+6^ weeks may predict adverse pregnancy outcome. These ultrasound features include: a) discordance in fetal nuchal translucency thickness (NT) with an increase in the recipient fetus [4, 5] and b) discordance in fetal crown rump length (CRL) measurements between the MC twins [5]. Although ultrasonographic features have a reasonable sensitivity and specificity in terms of allocating risk of severe TTTS, such screening is still associated with a significant false positive and false negative rate as the detection rate is only 52% [6].

We have recently reported significant differences in maternal serum between women with twin pregnancies complicated by TTTS, and twin pregnancies not complicated by TTTS but matched for gestational age [7]. These differences were seen in alpha-fetoprotein (αFP), β-hCG, plasma vascular endothelial growth factor (VEGF)-C, angiopoietin (Ang)-2 levels and the ratio of soluble vascular endothelial growth factor receptor-1 (sVEGFR-1) (also known as soluble fms-like tyrosine kinase-1. [sFlt-1]) to placental growth factor (PlGF) levels. We hypothesize that if these changes precede the development of the clinical syndrome, this may increase the sensitivity and specificity of detecting adverse pregnancy outcomes. The objective of this paper is to describe the aims and study design of our ongoing platform of work exploring complications in MC twin pregnancies.

## Methods

### Aims of study

The aim of our research is to improve knowledge of complications in MC twin pregnancies, and incorporate this knowledge into a predictive model in the future. Specifically we will investigate:If abnormal first-trimester ultrasound measurements (NT and CRL) are associated with the development of complications later in pregnancy.The effects that these complications and their treatment have on:angiogenic factors in maternal serum/plasmaplacental growth factors in maternal serum/plasmaangiogenic factors in amniotic fluidplacental growth factors in amniotic fluid

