#### Retrospective cohort

We will initially perform a retrospective study of stored maternal serum microbiology samples and Down Syndrome screening samples taken in the first trimester from MC twin pregnancies as part of routine booking at Birmingham Women’s NHS Foundation Trust. These samples are routinely stored for 2 years in the microbiology and clinical chemistry department, and equate to approximately 170 samples. We will measure maternal angiogenic factors and placental growth factors in these samples, collect first trimester ultrasound measurements (CRL and NT) and patient characteristics and pregnancy outcome data. As Down Syndrome screening samples are received from 31 sites in the UK, we will ask clinicians at these sites to assist in data collection using a pre-designed proforma. Where clinicians feel unable to help with data collection, we will visit the sites and collect the outcomes ourselves. The primary outcome will be whether participants developed a complication in pregnancy (TTTS, TAPS, sIUGR, single or double intrauterine demise) and the severity of these complications. Secondary outcomes will include delivery (gestation at delivery, mode of delivery, birth weight, condition of twins at delivery) and neonatal outcomes (admission to neonatal unit, diagnosis of comorbidity, particularly neurological). The maternal angiogenic factors and placental growth factors measured will be decided based on our preliminary work (see above) and a systematic review and individual patient data (IPD) meta-analysis (see PROSPERO CRD42015024975 for full protocol). As this is a retrospective study and the results of our study will not affect patient care, patients whose blood samples we are using in this retrospective study will not be consented or informed of the results. However, all women under the care of Birmingham Women’s NHS Foundation Trust are aware that the hospital is research active, and that their blood samples may be used in this way, and are given the option of opting out if they so wish. Samples from patients who have indicated that they do not want their samples to be used for research will be excluded from this study. This retrospective study will inform the subsequent prospective study.

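### The only specific biomarker aim is the effect of complications on the markers, although the hypothesis and first-trimester assays are predictive, and the cohort S comparison does not separate draws before diagnosis from draws after it

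*Protocol article*

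**What the plan says.** The Aims of study section has a general aim and two specific ones. The general aim is to learn about complications and to "incorporate this knowledge into a predictive model in the future". The first specific aim is predictive and concerns ultrasound: "If abnormal first-trimester ultrasound measurements (NT and CRL) are associated with the development of complications later in pregnancy". The second is the only one that names biomarkers: "The effects that these complications and their treatment have on" angiogenic and placental growth factors in maternal blood and amniotic fluid.

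Other sections put the biomarker question the other way round:

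- **Background:** "We hypothesize that if these changes precede the development of the clinical syndrome, this may increase the sensitivity and specificity of detecting adverse pregnancy outcomes".
- **Retrospective cohort:** the markers are measured in booking and "Down Syndrome screening samples taken in the first trimester from MC twin pregnancies". The primary outcome is whether a complication developed, and how severe it was.
- **Data management and data analyses:** serial serum biomarkers in cohort S are compared between women who later have a complication and women who do not.

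Cohort S is sampled at about 12, 16 and 20 weeks. The Background says that TTTS "usually occurs between 15 and 26 weeks".

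**The concern.** The stated aims and the planned work point in different directions for biomarkers. An aim about effects of a complication needs samples taken once the complication exists. An aim about prediction needs samples taken before it. The article writes down the first kind of aim for biomarkers but plans work of both kinds.

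The mismatch reaches the analysis. The cohort S comparison groups women by what eventually happens to them and uses all their serial draws. For a woman who develops TTTS, the 12-week draw comes before the usual onset window, but the 16- and 20-week draws may fall before or after diagnosis. If they are analysed together, a difference at 16 or 20 weeks cannot be assigned to either question. The Discussion says the results may inform a larger multi-centre study to build a prediction model. Such a study needs to know which markers differ before diagnosis, and a comparison that mixes in post-diagnosis samples could make a marker of established disease look like a predictor.

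**Working it through.** No power calculation is involved. The check is of consistency between sections, plus a count of the samples concerned.

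**1. The article's expected numbers (Expected number of participants)**

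- Cohort S: 7,900 × 0.02 = 158 multiple pregnancies a year; × 0.30 = 47.4 MC; × 0.70 = 33.18; − 5 = 28.18 a year; × 2 years = 56.36. The stated 56 is reproduced.
- Cohort C: 40 × 2 × 0.5 = 40 and 60 × 2 × 0.5 = 60. The stated 40–60 is reproduced.
- Retrospective cohort: about 170 samples of two types, not stated as women. Assumption: if every woman gave both types, 170 / 2 = 85 women. The range of 85 to 170 women exceeds both prospective cohorts throughout.

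**2. Which samples fit which biomarker question**

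| Samples | Timing against diagnosis | Fits the stated effects aim? | Fits the hypothesis? |
|---|---|---|---|
| Retrospective, first trimester (about 170) | Before the usual TTTS window | No, for TTTS | Yes |
| Cohort S, first draw (56) | Before the usual TTTS window | No, for TTTS | Yes |
| Cohort S, 16 and 20 weeks | Inside the window, either side | Only if after diagnosis | Only if before diagnosis |
| Cohort C, pre- and post-laser (40–60 women) | After diagnosis | Yes | No |

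The largest set of samples, and the first of three draws in cohort S, therefore serve the hypothesis but no specific biomarker aim.

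**3. Size of the ambiguous part of cohort S**

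- Planned draws: 56 × 3 = 168. First trimester: 56. At 16 and 20 weeks: 56 × 2 = 112.
- Expected TTTS at the Background's 10–15%: 56 × 0.10 = 5.6 to 56 × 0.15 = 8.4 women.
- Their 16- and 20-week draws: 2 × 5.6 = 11.2 to 2 × 8.4 = 16.8, so about 11 to 17.

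The article gives no distribution of onset within 15–26 weeks, so the share of these draws taken after diagnosis is unknown. It would be none if every case were diagnosed after the 20-week draw, and all if every case were diagnosed before the 16-week draw. This assumes that scheduled draws continue after diagnosis. The Prospective cohort section invites affected women into cohort C but does not say whether their remaining cohort S draws stop.

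The count covers TTTS only. The article gives no onset time for TAPS, sIUGR or intrauterine demise, so their draws cannot be placed in the same way.

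**4. Comparison with the retrospective cohort**

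At the same rates, the retrospective cohort would hold between 85 × 0.10 = 8.5 and 170 × 0.15 = 25.5 women with TTTS, all sampled in the first trimester. The timing ambiguity for TTTS is thus confined to the later cohort S draws.

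**The case against.** The strongest reply is that this is one loosely worded aim in a condensed article. The hypothesis gives the direction, the Retrospective cohort section gives first-trimester measurement and a later outcome, and the analysis section gives the cohort S comparison and logistic regression for association. The retrospective cohort also has other stated uses: its NT and CRL data serve the first specific aim, and its marker results inform what is measured prospectively. Rewording the aim would change no estimate.

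Much of this stands, and it rules out several stronger readings:

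- **That the aims concern effects only.** They do not. The ultrasound aim is predictive; the gap is in the biomarker aim.
- **That the predictive biomarker question is absent from the study.** It is not. The general aim looks to a future model, and a hypothesis, an outcome and a comparison for early markers are all stated. What is missing is a specific aim that matches them.
- **That a 12-week difference would be reported as an effect of the complication.** Nothing in the article says so.
- **That the stated direction is impossible for every early sample.** The onset window is given for TTTS alone, with the word usually, so the argument holds for first-trimester samples and TTTS. It does not extend to the 16- and 20-week draws or to the other complications.

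The reply does not deal with the mixed timing of the later cohort S draws. The analysis section does separate cohort S by later complication, cohort C against cohort S controls, and pre- against post-laser. It does not separate draws before diagnosis from draws after it within cohort S. Nor can the aims be left to a fuller document, since the Background says that describing the aims and design is the purpose of this article, and the aims it states conflict with its other sections.

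**Conclusion.** The point holds. The sole specific biomarker aim does not match the hypothesis, the retrospective primary outcome or the cohort S comparison, and the cohort S comparison leaves prediction and established disease unseparated at 16 and 20 weeks.

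No figure in the article is wrong. The inconsistency in the aim touches all retrospective marker assays and the 56 first draws in cohort S, but by itself changes no result. The analytic consequence is smaller and more specific: about 11 to 17 draws from about 6 to 8 expected TTTS cases in cohort S. With so few cases, whether those draws came before or after diagnosis could decide what the comparison shows.

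This rests on the article's 10–15% TTTS rate, its expected 56 women each giving three draws, and scheduled sampling continuing after diagnosis. It should be changed because the remedy is nearly free and determines what may be concluded from a difference.

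**What to change.** - **Aims of study:** add a specific aim on whether angiogenic and placental growth factors in samples drawn before any complication is diagnosed (the retrospective first-trimester samples and pre-diagnosis cohort S draws) are associated with later complications. Limit the effects aim, for affected women, to post-diagnosis samples and the pre/post-laser comparison.
- **Data management and data analyses:** restrict the cohort S comparison by later complication to draws taken before diagnosis, and state which aim each comparison serves. Because the 16- and 20-week draws are taken at routine scan visits, also state how a draw on the day of diagnosis is classed.

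Which aim is primary is for the sponsor to decide.

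The change takes a few lines and needs no new samples; it does need the date of diagnosis for each complication in cohort S. The downside is fewer case samples at 16 and 20 weeks in the predictive comparison. At the extreme, all of the 11 to 17 TTTS draws would be lost from it, leaving the first-trimester draws for those women.

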### Study design

This cohort study has both retrospective and prospective elements. There will be 1 retrospectively recruited first-trimester cohort, 1 prospectively recruited “screening” cohort, and 1 prospectively recruited “complicated” cohort. In all aspects of the work monochorionicity must have been confirmed using the ‘T’ sign on first-trimester ultrasound scan.

#### Retrospective cohort

We will initially perform a retrospective study of stored maternal serum microbiology samples and Down Syndrome screening samples taken in the first trimester from MC twin pregnancies as part of routine booking at Birmingham Women’s NHS Foundation Trust. These samples are routinely stored for 2 years in the microbiology and clinical chemistry department, and equate to approximately 170 samples. We will measure maternal angiogenic factors and placental growth factors in these samples, collect first trimester ultrasound measurements (CRL and NT) and patient characteristics and pregnancy outcome data. As Down Syndrome screening samples are received from 31 sites in the UK, we will ask clinicians at these sites to assist in data collection using a pre-designed proforma. Where clinicians feel unable to help with data collection, we will visit the sites and collect the outcomes ourselves. The primary outcome will be whether participants developed a complication in pregnancy (TTTS, TAPS, sIUGR, single or double intrauterine demise) and the severity of these complications. Secondary outcomes will include delivery (gestation at delivery, mode of delivery, birth weight, condition of twins at delivery) and neonatal outcomes (admission to neonatal unit, diagnosis of comorbidity, particularly neurological). The maternal angiogenic factors and placental growth factors measured will be decided based on our preliminary work (see above) and a systematic review and individual patient data (IPD) meta-analysis (see PROSPERO CRD42015024975 for full protocol). As this is a retrospective study and the results of our study will not affect patient care, patients whose blood samples we are using in this retrospective study will not be consented or informed of the results. However, all women under the care of Birmingham Women’s NHS Foundation Trust are aware that the hospital is research active, and that their blood samples may be used in this way, and are given the option of opting out if they so wish. Samples from patients who have indicated that they do not want their samples to be used for research will be excluded from this study. This retrospective study will inform the subsequent prospective study.

#### Prospective cohort

The prospective study will run over 2 years (August 2015–August 2017) and there will be 2 cohorts: a “screening” MC twin cohort (Cohort S), and a cohort who have developed complications (Cohort C) (see Fig. 1). In both cohorts, informed written consent will be obtained. The “screening” cohort (Cohort S) will be approached in the ‘multiples’ antenatal clinic where all twin pregnancies are managed at Birmingham Women’s NHS Foundation Trust. We will ask participants with confirmed MC twin pregnancies to consent to 2 extra bottles of blood being taken during their routine Down Syndrome blood test or booking blood tests, and for permission to record their first trimester ultrasound measurements, and access the above outcome data as specified in the retrospective study. We will then repeat the blood sampling at 16 weeks and 20 weeks gestation when they attend for routine ultrasound scans. If the participant does not develop any complications, this will be the end of her involvement in the study and we will just collect the outcome data. However, if she develops a complication (e.g. TTTS, TAPS, sIUGR, single intrauterine demise) she will be invited and consented to enter the second prospective “complicated” cohort.

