### Data management and data analyses

At recruitment, each participant will receive a unique study identifier to allow linkage of data. Data will be collected using a purposely designed proforma (as per the retrospective cohort) and manually input onto a secure electronic database. Hard-copies of data will be kept in a locked filing cabinet, in a swipe-card access department at Birmingham Women’s NHS Foundation Trust. We will ensure that we remain compliant with the Trust’s Information Governance policies at all times.

Descriptive data will be reported. First trimester ultrasound measurements (NT and CRL) and serial serum biomarkers will be compared between participants in cohort S who go on to develop complications, and participants in cohort S who do not develop complications. The serum biomarker results from the 16 and 20 week blood samples from participants in cohort S will also act as the control group for cohort C participants. Additionally serum and amniotic fluid biomarkers will be compared longitudinally (i.e. pre- and post-FLA) for each participant in cohort C, to evaluate the potential effect of FLA on the biomarkers. The appropriate statistical tests will be used. Chi-squared will be used for categorical variables, and student’s t-test (paired and unpaired where appropriate) for continuous variables. Logistic regression models will be created to assess the association between variables and outcomes and presented as odds ratios (OR) with a 95% confidence interval (CI). Different cut-offs will be used for TTTS (Quintero staging) and sIUGR (EFW <10^th^ centile, <5^th^ centile).

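### First-trimester markers come from two kinds of sample with no gestational window and are compared without stated control for gestation: modest precision loss in Cohort S, possible confounding in the retrospective cohort

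*Protocol article*

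**What the plan says.** All places are in the protocol article.

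- **Abstract, Methods.** Cohort S is described as having "serial maternal blood sampling at 12, 16 and 20 weeks".
- **Prospective cohort.** Women are asked to agree to "2 extra bottles of blood being taken during their routine Down Syndrome blood test or booking blood tests". No range of weeks is given for this draw. The later draws are fixed: "We will then repeat the blood sampling at 16 weeks and 20 weeks gestation when they attend for routine ultrasound scans".
- **Study design.** In every part of the work, "monochorionicity must have been confirmed using the ‘T’ sign on first-trimester ultrasound scan".
- **Retrospective cohort.** The material is "stored maternal serum microbiology samples and Down Syndrome screening samples taken in the first trimester", about 170 samples in all. The Down screening samples reach the laboratory from 31 UK sites.
- **Data management and data analyses.** Markers in Cohort S are compared between women who do and do not go on to a complication. The named test is the "t-test (paired and unpaired where appropriate) for continuous variables". Logistic regression is also planned, with covariates not listed. Neither mentions gestation at sampling.
- **Background.** In the authors' earlier comparison, the twin pregnancies without TTTS were different in outcome "but matched for gestational age".

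**The concern.** The hypothesis is that marker changes precede the clinical syndrome, so the first-trimester contrast is central. If a marker's level drifts with gestation, a sample taken at one visit is not interchangeable with one taken at another. The authors controlled gestation by design in their preliminary work, and the plan as written does not carry that control into this contrast.

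Two different things could follow:

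- If draw timing is unrelated to outcome, the drift is extra noise. That costs precision in a study whose Discussion already concedes that small numbers may give false negatives.
- If draw timing is related to outcome, the drift becomes bias.

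The retrospective results, together with the preliminary work and the individual patient data meta-analysis, decide which markers are measured prospectively. A distorted marker there could be carried forward or wrongly dropped.

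**Working it through.** **The plan's own figure.** Expected Cohort S size: 7,900 × 0.02 = 158; × 0.30 = 47.4; × 0.70 = 33.2; − 5 = 28.2 per year; × 2 = 56.4. The stated 56 reproduces. It is a feasibility count, and the document gives no SD, effect size or power.

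**Inputs from the document.** N = 56 in Cohort S; about 170 retrospective samples; TTTS in 10–15% of monochorionic twins, so 56 × 0.10 to 56 × 0.15 = 5.6 to 8.4 cases; first-trimester ultrasound screening at 11 to 13+6 weeks (Background).

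**Assumptions (none is in the document).** Slope b of a log marker: 0.1 to 0.3 within-gestation SD per week. SD of gestation at draw, g, for a uniform spread of draws:

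- 11 to 13+6 weeks: (20/7)/√12 = 0.82 weeks
- 8 to 13+6 weeks: (41/7)/√12 = 1.69 weeks

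**1. Precision lost in Cohort S.** R² = (bg)²/(1 + (bg)²), and controlling for gestation multiplies the interval width by √(1 − R²).

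| g (weeks) | b | R² | Interval shortens by |
|---|---|---|---|
| 0.82 | 0.1 | 0.007 | 0.3% |
| 0.82 | 0.3 | 0.057 | 2.9% |
| 1.69 | 0.1 | 0.028 | 1.4% |
| 1.69 | 0.3 | 0.204 | 10.8% |

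As power, for an assumed true difference of 0.8 SD, two-sided 5%, 15% complicated (8.4 against 47.6 women): 0.57 with gestation controlled. Uncontrolled, it is 0.57 to 0.55 for the narrow window and 0.56 to 0.48 for the wide one, over the same slopes.

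**2. Chance imbalance in Cohort S.** The SE of the difference in mean gestation is g√(1/n₁ + 1/n₀).

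- 6 against 50: 0.82 × 0.432 = 0.35 weeks
- 8 against 48: 0.82 × 0.382 = 0.31 weeks

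Multiplied by b, a one-SE imbalance moves the marker difference by 0.1 × 0.31 = 0.03 SD to 0.3 × 0.35 = 0.11 SD. The SE of the marker difference itself is at least 0.38 to 0.43 SD. This imbalance is already part of the t-test's standard error, so the type I error stays at 0.05.

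**3. What a systematic difference would do.** Let mean gestation at draw differ by d weeks between outcome groups. The bias is bd, the standard error is √(1 + (bg)²) × √(1/n₁ + 1/n₀), and with m = bd/SE the type I error is 1 − Φ(1.96 − m) + Φ(−1.96 − m).

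| Setting (15% complicated) | b | d = 0 | d = 0.5 | d = 1 |
|---|---|---|---|---|
| 56 women, g = 0.82 | 0.1 | 0.05 | 0.05 | 0.06 |
| 56 women, g = 0.82 | 0.3 | 0.05 | 0.07 | 0.12 |
| 170 samples (25.5 against 144.5), g = 1.69 | 0.1 | 0.05 | 0.06 | 0.07 |
| 170 samples (25.5 against 144.5), g = 1.69 | 0.3 | 0.05 | 0.10 | 0.24 |

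The 170-sample rows assume one sample per woman, independent samples, and the same t-test in the retrospective cohort. The value of d there is unknown.

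**The case against.** A reader might infer that the plan analyses raw levels, or that gestation is mixed with the outcome contrast in Cohort S and distorts it. The document supports neither.

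- **Raw is not stated.** A journal article may leave transformation and covariates to a fuller plan, and the logistic models could include gestation. This stands. What remains is that the text gives two descriptions of one draw and names an unadjusted test for the comparison.
- **No link between timing and outcome in Cohort S.** Blood is drawn before the outcome is known, and nothing ties the choice of visit to a later complication. Chance imbalance is ordinary sampling error. This stands.
- **Very early draws are unlikely in Cohort S.** Women are recruited with monochorionicity already confirmed on a first-trimester scan, and the count of 56 includes only those accepting Down screening. This stands, so the narrow window is the fairer reading there.
- **More cases than TTTS alone.** The outcome also covers TAPS, sIUGR and fetal demise, so the complicated group may be larger and chance imbalance smaller. This stands.
- **The preliminary matching proves no first-trimester slope.** TTTS usually arises at 15 to 26 weeks, so matching there says little about drift before 14 weeks. This stands, and it is why every slope above is an assumption.

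These points do not clear the retrospective cohort. There, two sample types and 31 sites are put together, and source, site and gestation may vary together. However, the analysis section does not name the test for that contrast, and marker choice does not rest on it alone.

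**Conclusion.** The concern holds in a limited form. First-trimester samples come from more than one occasion or source with no stated window, the 12-week label does not fit the detailed description, and no control for gestation at sampling is stated.

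In Cohort S the expected consequence is modest lost precision: an interval about 0.3% to 3% wider than it need be for slopes of 0.1 to 0.3 SD per week within 11 to 13+6 weeks, and about 1% to 11% if draws spread over 8 to 13+6 weeks. Type I error is not inflated unless timing differs systematically by outcome, which no passage suggests.

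In the retrospective cohort confounding is possible but not demonstrated. It requires sample source or site to be related both to gestation at draw and to complication rate. If that produced a one-week difference, the type I error would be 0.07 to 0.24 under the assumptions above. The change is worth making because it is cheap and because these results inform the prospective marker list.

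**What to change.** 1. Reconcile the abstract with the Prospective cohort section, and state the actual range of gestations covered by the first sample.
2. Record exact gestation at draw and sample source for every first-trimester sample. The article lists CRL among the data collected but does not mention a sampling date, so its availability for stored samples needs checking.
3. Use one sample per woman where both a microbiology and a Down screening sample exist, chosen by a rule set in advance and blind to outcome.
4. In the first-trimester marker comparisons (retrospective and Cohort S), analyse log markers adjusted for, or standardised to, gestation at sampling. In the retrospective cohort, also account for sample source. Multiples of the median are one option and a covariate is another.
5. Date gestation by one pre-specified rule. If CRL is used, say which twin's, because CRL discordance is itself a predictor under study.

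**Cost.** A few lines of text, slightly more analysis work, and no extra participants. The real price is one or two extra terms, or medians estimated from few women, in a small sample.
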